### Recruitment {15}

Recruitment for the CLI groups will be conducted through four networks: (1) general practitioners of Extramural Leiden University Medical Center Academic Network; (2) general practitioners of ‘Huisartsenorganisatie West-Friesland’; (3) the Diabetes Care System [92]; and (4) CooL-MiGuide. If necessary, additional recruitment will be carried out through other general practitioners or via social media.

## Assignment of interventions: allocation

### Sequence generation {16a}

A minimum of ten groups will be scheduled for the pragmatic trial. These groups will be cluster-randomized (1:1) to either the TIMED CLI or the standard CLI using a randomization list (block size of 4) made by an independent statistician using *Randomizr* packages (version 1.0.0) in RStudio (version 4.4.0).

### Concealment mechanism {16b}

Randomization of each group will be performed by the coordinating researcher after the enrolment of that group is completed. During the enrolment period and at the time of group allocation, both the participants and scheduling staff will remain unaware of the assigned intervention, as randomization has not been performed at that point.

### Implementation {16c}

Prior to randomization, participants are assigned to a group based on their personal scheduling preferences for time and day by scheduling staff.

## Assignment of interventions: blinding

### Who will be blinded {17a}

Blinding of both participants and lifestyle coaches is not feasible due to the study design, as both are aware of whether additional education on timing of lifestyle factors is provided. To minimize bias, endpoint evaluation will be performed by an independent statistician.

### Procedure for unblinding if needed {17b}

Since the research team and participants are not blinded to the treatment allocation, unblinding procedures are not needed.

## Data collection and management

### Plans for assessment and collection of outcomes {18a}

Participants will receive a home kit to measure their fasting glucose and HbA1c. HbA1c levels will be assessed using a high-performance liquid chromatography assay at the Amsterdam UMC – VUmc clinical laboratory, and fasting glucose will be measured using the Contour Plus Blue glucose monitor. Lab results will be entered in the electronic case report forms (eCRF) in Castor EDC as soon as they are determined by the laboratory. Questionnaires will be completed by the participants using Castor EDC. Data extracted from the MiGuide platform, including anthropometric measures, will also be incorporated.

### Plans to promote participant retention and complete follow-up {18b}

Since we are recruiting participants that have already committed to joining a CLI, we anticipate that these individuals will be committed to the CLI. To promote participant retention and ensure complete follow-up, the research burden has been intentionally minimized, reflecting the pragmatic nature of the trial. Participants will receive all data collection materials at home, including self-addressed return envelopes, and will complete a limited number of online questionnaires from home. Reminder emails will be sent at each data collection time point, and participants who are unable to fingerpick themselves may request assistance from the research team or their local general practitioner.

### Data management {19}

We will use Castor EDC as a clinical data management system to capture all collected data in eCRFs [93]. Data validation checks and notifications are embedded in the eCRF to ensure correct data entry.

### Confidentiality {27}

The handling of personal data complies with the Dutch Personal Data Protection Act (AVG/GDPR). The data of all participants that will participate in the present study will be coded. All participants recruited from the Diabetes Care System have an identification number, consisting of five numbers, obtained during previous studies. All other participants will receive a new identification number. These numbers cannot be traced to the person without the key, which is stored separately. The key document is only available to the participating investigators. Participants can request the information stored in their eCRF.

### Plans for collection, laboratory evaluation and storage of biological specimens for genetic or molecular analysis in this trial/future use {33}

Biological samples collected during this study will be analyzed during the study. All remaining materials will be destroyed afterwards.

## Statistical methods

### Statistical methods for primary and secondary outcomes {20a}

Baseline characteristics will be described by intervention arm as mean ± standard deviation, median and interquartile range (if not normally distributed), or numbers and percentages if categorical. Statistical analyses will be performed using RStudio. An intention-to-treat analysis will be performed for both primary and secondary outcomes using multiple linear mixed models to compare changes between baseline, and at 3, and 9 months and compare between intervention arms. For BMI and waist circumference, effects will also be estimated at 24 months. The models will account for clustering within CLI groups, and outcomes that are not normally distributed will be log-transformed prior to analysis.

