### Sample size {14}

To our knowledge, no previous study has compared effects of education on timing of a combination of different lifestyle behaviours, with routine care CLI on any outcome. We could thus not use such studies to inform our power calculation. Therefore, we based our sample size calculation on our primary outcome of BMI based on a study comparing caloric restriction with and without time-restricted eating in participants with obesity [91]. This study by Liu et al. [91] found a 0.7 kg/m^2^ greater reduction in BMI in time-restricted eating after 12 months compared to caloric restriction alone. Although cluster randomization will be used, we expect minimal within-cluster correlation, since the clustering is solely on participants’ personal schedules rather than shared characteristics such as place of residence. To further minimize potential correlation, groups will be scheduled on different days and at different times of day. To detect a difference of 0.7 ± 0.9 kg/m^2^ in BMI with an *α* of 0.05, and *β* of 0.1, an intraclass correlation coefficient of 0.02, and a cluster size of 8–12 participants, we calculated that 45 participants per group are required. Accounting for 10% attrition rate, a total of 50 participants per group will be enrolled.

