### Methods in analysis to handle protocol non-adherence and any statistical methods to handle missing data {20c}

Compliance to the standard CLI or TIMED CLI will be tested based on the percentage of completion of modules on the MiGuide platform and attendance to the group meetings. Both completion of ≥ 80% of the modules, as well as ≥ 80% of the sessions, will be defined as compliant [94]. Both intention-to-treat and per-protocol analyses will be performed based on this compliance to the CLI. Additionally, adherence to the timed lifestyle behaviours will be self-reported and based on the timing of eating questionnaire, sleep questionnaire, and timing of physical activity questionnaire. These questionnaires will provide insight in adherence to the timed recommendations for all participants, both at baseline as well as changes during the follow-up period. To assess adherence, several sensitivity analyses will be conducted, comparing the timing of a certain lifestyle behaviour between baseline and follow-up. For example, participants who are already engaging in physical activity predominantly in the afternoon or evening, or those who transition towards physical activity in the afternoon or evening over the course of the study, will be considered adherent to the physical activity timing recommendations. This approach enables us to capture partial adherence to the different behaviours.

Fidelity of the coaches is assessed by checking the presentations that were given by the coaches during the session, which are uploaded to the MiGuide platform for the participants. When sessions are cancelled (due to unforeseen circumstances) and not rescheduled, this will be noted in a deviation form protocol by the researchers. Contamination of the timed advices between the TIMED CLI and standard CLI will be assessed by comparing the compliance results and adherence results. Furthermore, mixed model analysis will be used, which is able to account for missingness. We will therefore not do any imputation for missing data. Imbalances in participants’ characteristics between groups will not be tested statistically. However, clinically relevant imbalances will be addressed through sensitivity analyses that adjust for these variables.

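### The log-transform rule does not exempt BMI and gives no criterion, so the data could move the primary result off the kg/m² scale on which the trial was sized; baseline adjustment should also be stated.

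*Protocol article*

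**What the plan says.** Statistical methods {20a} states that "An intention-to-treat analysis will be performed for both primary and secondary outcomes". The method is described there as "using multiple linear mixed models to compare changes between baseline, and at 3, and 9 months and compare between intervention arms". It adds that "The models will account for clustering within CLI groups" and that "outcomes that are not normally distributed will be log-transformed prior to analysis". The last clause applies to every outcome in the section, BMI included. It gives no test, plot or threshold, and does not say which quantity has to be normal. No baseline term or covariate is named.

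The section on non-adherence and missing data {20c} says that "Imbalances in participants’ characteristics between groups will not be tested statistically", and that "clinically relevant imbalances will be addressed through sensitivity analyses that adjust for these variables".

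Sample size {14} fixes the planning effect on the absolute scale: "To detect a difference of 0.7 ± 0.9 kg/m^2^ in BMI". The source is a trial that found a "greater reduction in BMI in time-restricted eating after 12 months compared to caloric restriction alone". Table 1 admits people with BMI of at least 25 kg/m², those below 30 only with a comorbid condition.

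**The concern.** A linear mixed model needs roughly normal residuals and random effects. It does not need the outcome itself to be normal. Read literally, the rule looks at the outcome. In a sample cut off at BMI 25 the raw values may well be right-skewed even where within-person changes are close to normal.

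If the rule fires for BMI, the primary effect becomes a ratio. It can then no longer be read directly against the 0.7 kg/m² used for sizing, nor easily against other lifestyle studies, although such comparability is one of the reasons the Outcomes section gives for choosing BMI. Which effect measure is reported would depend on a distribution check that the protocol does not define.

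A smaller, related matter is that adjustment for the baseline value is not stated. It costs almost nothing and can help the noisier secondary outcomes.

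**Working it through.** **Planning figure.** Inputs from Sample size {14}: difference 0.7, SD 0.9, alpha 0.05 (two-sided assumed), power 90%, ICC 0.02, cluster size 8–12.
- Individually randomised n = 2 × [0.9 × (1.960 + 1.282) / 0.7]² = 34.7, so 35 per arm (36 with the t distribution).
- Design effect at 12 per group = 1 + 11 × 0.02 = 1.22, giving 43 (normal) or 44 (t) per arm, close to the stated 45.
- 45 / 0.9 = 50, as stated.

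The trial is therefore sized on an absolute kg/m² difference. An SD of 0.9 can only sensibly be the SD of change, since cross-sectional BMI varies far more.

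**What the log scale does to the effect measure.**
- 0.7/25 = 2.8%; 0.7/33 = 2.1%; 0.7/45 = 1.6%.
- A common ratio matching 0.7 kg/m² at BMI 33 means 25 × 0.7/33 = 0.53 kg/m² at BMI 25 and 45 × 0.7/33 = 0.95 kg/m² at BMI 45.

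**Whether the rule could fire.** The protocol gives no BMI distribution, so these inputs are assumed: normal BMI cut at 25, 90 participants, Shapiro-Wilk at 5%, 2,000 simulated trials per setting.

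| Mean, SD before cutting | Raw BMI fails |
|---|---|
| 30, 4 | 65% |
| 32, 4 | 20% |
| 33, 5 | 30% |
| 35, 5 | 10% |

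Normally distributed changes with SD 0.9 fail in about 5%, as expected. Whether BMI is logged thus depends heavily on which quantity is checked.

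**Effect on false positives.** Null simulation: 4,000 trials, 50 per arm, individual level without clustering, BMI mean 33 and SD 5 cut at 25, SD of change 0.9.
- Absolute change 5.4%, log change 5.9%, smaller of the two p-values 6.5%.
- The scales disagree on significance in 1.7% of trials.
- Simulation error near 5% is √(0.05 × 0.95/4000), about 0.3 percentage points.

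**Baseline adjustment.** With equal variances at baseline and follow-up, the variance of the adjusted contrast relative to the change score is (1 + ρ)/2, where ρ = 1 − SD_change²/(2 × SD²).
- BMI, SD of change 0.9, assumed cross-sectional SD 3 to 6: ρ = 1 − 0.81/18 = 0.955 to 1 − 0.81/72 = 0.989. The ratio is 0.978 to 0.994, a saving of about 0.6–2.3%.
- With 45 per arm in groups of 12, power moves from 91.6% to 91.8–92.2%. Required n falls from 42.4 to 41.4–42.1 per arm.
- Secondary outcomes at assumed ρ of 0.5, 0.7 and 0.9: savings of 25%, 15% and 5%.

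**Chance baseline imbalance in BMI.** At an assumed SD of 5 and groups of 10 (design effect 1.18), the standard error of the baseline difference is 5 × √(2 × 1.18/50) = 1.09. A gap above 0.7 kg/m² then has about a 52% chance. In an unadjusted change analysis only (1 − ρ) of the gap carries over: with ρ = 1 − 0.81/50 = 0.984, a gap of 0.7 shifts the effect by 0.016 × 0.7 = 0.011 kg/m², or 1.6% of the target difference.

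**The case against.** Several stronger readings are tempting, and the document does not support them.

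- **That the primary analysis is unadjusted.** This would be an inference from silence. The wording fits a longitudinal model with baseline among the repeated measurements. With baseline means constrained equal across arms, such a model comes close to ANCOVA. The full model specification is commonly left to an analysis plan, which is not shown. This objection stands.
- **That covariates picked after looking at the data decide the primary result.** They do not. {20c} confines that adjustment to sensitivity analyses and rules out significance tests of imbalance. This also stands.
- **That precision on BMI suffers, or that chance imbalance biases it materially.** On the protocol's own SD of 0.9 both effects are negligible, as computed above. The larger savings for secondary outcomes rest on correlations that the protocol does not give.
- **That the log rule seriously inflates false positives.** The simulation shows only a small rise, even under the worst use of the rule.

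It can also be said that the log rule may be meant for residuals or changes, in which case BMI would seldom trigger it, and that the skewness is inferred from eligibility rather than observed. Both are fair. But the sentence as written speaks of the outcomes, exempts none of them and leaves the choice open. An analysis plan that fixed BMI in kg/m² whatever its distribution would have to depart from it. That part of the concern survives.

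**Conclusion.** The concern holds for the transformation rule. The protocol states a rule that can change the primary effect measure from a kg/m² difference to a ratio, on an undefined criterion, while the sample size rests on an absolute 0.7 kg/m². The main harm is an effect measure that is not fixed in advance and a result that may not be comparable with its planning value; the rise in type I error is small (6.5% against 5.4–5.9%). How likely the rule is to fire depends on assumed BMI distributions and ranged from 10% to 65% when raw values were tested.

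The absence of a stated baseline term supports a recommendation to state it, not a claim of error. Its value is negligible for BMI (about 0.6–2.3% of variance, at most one participant per arm, under one percentage point of power) and possibly 5–25% of variance for secondary outcomes. These figures assume equal variances at both times, a cross-sectional BMI SD of 3–6, and secondary-outcome correlations of 0.5–0.9. The sample size figures reproduce and are not in question here.

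**What to change.** In the protocol or analysis plan:

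1. State that BMI and waist circumference are analysed in natural units (kg/m² and cm) whatever their marginal distribution.
2. Judge normality on model residuals. Use a log scale only for outcomes named in advance (fasting glucose is a candidate) or as a sensitivity analysis.
3. State that the primary and secondary models adjust for the baseline value of the outcome, as a covariate or by constraining baseline means to be equal across arms.
4. Name any further covariates before data by arm are seen. Which ones is for the trial team to choose; the protocol gives no figures that favour a particular set. The imbalance rule in {20c} can stay as a sensitivity analysis.

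The cost is wording and at most a few degrees of freedom. The baseline values of BMI, waist circumference, glucose, HbA1c and quality of life are already collected. Trial status expects 9-month collection to end in April 2026, so the wording should be settled before any outcome data are examined by arm.

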### Interim analyses {21b}

Interim analyses will not be performed for this study.

### Methods for additional analyses (e.g. subgroup analyses) {20b}

Additional exploratory analyses will be performed to get a better understanding of the effectiveness of the intervention in certain subgroups. Therefore, analyses will be stratified to evaluate whether certain subgroups (e.g., early versus late chronotype, participants with versus without type 2 diabetes) benefit more from the intervention, compared to others. In addition, a greater shift towards desired timing behaviours will be associated with metabolic improvements, to see whether a dose–response relationship can be found. Furthermore, acceptability of the added education will be assessed by comparing the acceptability questionnaire between the standard CLI and TIMED CLI. In addition, the results of the standard CLI and TIMED CLI will be compared with an additional arm from the general care database DIAMANT. It will enable us to distinguish effects attributable to the standard CLI from those reflecting additive effects of the timed education. This is only for exploratory purposes and will not be used to draw any causal conclusions on the effect of the standard CLI itself.

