### Trial design {8}

This study is a two-armed, cluster-randomized, superiority, pragmatic trial with two comparator groups. At least 10 groups will be cluster-randomized 1:1 to one of the intervention arms: the standard CLI or the TIMED CLI, with added education on timing of lifestyle behaviours. In addition, an additional observational arm will be used for exploratory analyses to distinguish results attributable to the standard CLI from those reflecting additive effects of the timed education in the TIMED CLI. To keep the trial pragmatic and reduce participant burden, instead of active recruitment of a waiting list control group, 800 participants from the routine care database called the Diabetes Management and Treatment (*DIAMANT*) cohort will be included for exploratory purposes only. These exploratory analyses will enable us to distinguish effects attributable to the standard CLI from those reflecting additive effects of the timed education. This cohort, initially for patients with diabetes, recently expanded with all patients with risk factors of type 2 diabetes: cardiometabolic diseases, overweight or obesity, dementia, and depression. These participants will be matched 8:1 based on age, sex, comorbid condition, and postal codes with participants in the two intervention arms.

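### The stratified subgroup analyses give no estimate of the difference in effect between subgroups, which is what a claim of greater benefit needs

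*Protocol article*

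**What the plan says.** Under *Methods for additional analyses {20b}*, the protocol article introduces the subgroup work as exploratory: "Additional exploratory analyses will be performed to get a better understanding of the effectiveness of the intervention in certain subgroups". The next sentence gives the method: "analyses will be stratified to evaluate whether certain subgroups (e.g., early versus late chronotype, participants with versus without type 2 diabetes) benefit more". The two subgroup pairs are offered as examples, and no other method for comparing subgroups is named.

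The section on statistical methods for primary and secondary outcomes {20a} describes linear mixed models that compare the arms over time and account for clustering within counselling groups. It names no subgroup term. No treatment-by-subgroup interaction appears anywhere in the article.

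The planning figures are under *Sample size {14}*: "To detect a difference of 0.7 ± 0.9 kg/m^2^ in BMI", "an intraclass correlation coefficient of 0.02", "a cluster size of 8–12 participants", "we calculated that 45 participants per group are required" and "Accounting for 10% attrition rate, a total of 50 participants per group will be enrolled". On the number of clusters, *Trial design {8}* says "At least 10 groups will be cluster-randomized 1:1 to one of the intervention arms".

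**The concern.** Whether one subgroup benefits more than another is a question about the difference between two treatment effects. Separate models in each stratum estimate each effect but not the difference, so the analysis as described stops one step short of its own question.

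That gap tends to be filled informally, by noting that one stratum reached significance and the other did not. With about 45 evaluable participants per arm, each stratum is too small for this to be safe. Two strata with the same true effect can easily fall on opposite sides of 0.05. At stake is a report that the timing education helps, say, late chronotypes or people with type 2 diabetes only, when the data do not show any difference.

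**Working it through.** **Inputs.** From *Sample size {14}*: difference 0.7 kg/m², SD 0.9 (taken as the SD of the outcome compared between arms), α 0.05 (two-sided assumed, as the sidedness is not stated), β 0.1, ICC 0.02, cluster size 8–12, 45 evaluable per arm. Subgroup prevalences are not given, so the splits below are assumptions.

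**The plan's own figure.** Without clustering, n = 2 × [(1.960 + 1.282) × 0.9 / 0.7]² = 34.7, so 35 per arm (35.7, so 36, with the t distribution). The design effect is 1 + (m − 1) × 0.02. At m = 12 it is 1.22, giving 43 or 44 per arm. At m = 9 it is 1.16, giving 35.7 × 1.16 = 41.4, which rounds up to 5 whole clusters of 9, or 45. Then 45 / 0.9 = 50. The stated size is reproduced closely enough to use as it stands.

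**Power in each stratum when the true effect is 0.7 in both (clusters of 9).**

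- Full design effect, 50:50 split. Overall SE = 0.9 × √(2 × 1.16 / 45) = 0.204. Half-sample SE = 0.204 × √2 = 0.289, z = 0.7 / 0.289 = 2.42, power = Φ(2.42 − 1.96) = 68%.
- Design effect for the stratum's share of the cluster, 50:50 split. 1 + (4.5 − 1) × 0.02 = 1.07, SE = 0.9 × √(2 × 1.07 / 22.5) = 0.278, z = 2.52, power 71%.
- The same, 30:70 split. Smaller stratum: 13.5 per arm, design effect 1.034, SE 0.352, z 1.99, power 51%. Larger stratum: 31.5 per arm, design effect 1.106, SE 0.239, z 2.94, power 84%.

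**Chance that exactly one stratum is significant.** Treating the strata as independent, this is pA(1 − pB) + pB(1 − pA).

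| Split (assumed) | Powers | Exactly one significant |
|---|---|---|
| 50:50, full design effect | 68%, 68% | 2 × 0.678 × 0.322 = 44% |
| 50:50, within-stratum design effect | 71%, 71% | 2 × 0.713 × 0.287 = 41% |
| 30:70, within-stratum design effect | 51%, 84% | 0.511 × 0.165 + 0.835 × 0.489 = 49% |

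Both strata can lie within the same counselling groups and so share cluster effects. A simulation that allows for this (5 clusters of 9 per arm, ICC 0.02, 40,000 runs) gave 39% for a 4:5 split within clusters and 45% for 3:6.

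**How this depends on the true effect.** With a common effect of 0.35 the rate is about 35–37%. With no effect in either stratum it is 2 × 0.05 × 0.95 = 9.5%; the simulation gave 9–10%. An interaction test at two-sided 0.05 declared a difference in 4.9–5.1% of simulated trials in every one of these cases.

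**Power of the interaction test.** For an interaction of 0.7, SE = 0.9 × √(2 / (45f) + 2 / (45(1 − f))), where f is the share in the smaller subgroup. Cluster effects largely cancel in this contrast when both subgroups occur within clusters.

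- f = 0.5: SE 0.379, ratio 1.84, power 45%
- f = 0.3: SE 0.414, ratio 1.69, power 39%
- f = 0.2: SE 0.474, ratio 1.48, power 31%

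**The case against.** The article is a condensed account, the SAP is not shown, and the subgroup analyses are labelled exploratory. A reader might infer that the trial has chosen stratification in preference to interaction tests. The text does not support that: it is silent on interactions and does not exclude them. It also does not say that strata will be compared by significance. If stratum estimates and intervals were set side by side, the 41–50% figures would not apply, and an approximate difference could be derived from the two estimates and their standard errors.

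A reader might also infer that false differences will be frequent whenever the effect is equal in both subgroups. That is too broad, because equal effects include no effect at all, where the rate is about 9–10%. Nor does anything in the article say that the programme would be targeted by subgroup on these results, so a wrongly targeted programme is conjecture.

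These limits stand. What remains is that the article does name a method for a comparative question, and that method does not deliver the comparison. The exploratory label lowers the stakes but does not close the gap. Differencing two separately fitted strata is also less clean here than in an individually randomised trial, because the strata can share counselling groups.

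The interaction test's own low power is a fair criticism. It is a reason to report an interval and state the imprecision, and does not justify relying on separate p-values.

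**Conclusion.** The point holds as a fault of method in an exploratory analysis. Stratification alone cannot support a statement that one subgroup benefits more than another.

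If strata were compared by their separate p-values and the planning effect were true in both, a contrast of one significant and one non-significant stratum would arise about 41–44% of the time at 50:50 and about 50% at 30:70, against about 5% for an interaction test. These figures rest on the protocol's effect, SD, ICC and evaluable sample size, two-sided testing, assumed splits, and a comparison rule that the article does not state. They shrink as the common effect shrinks. The primary comparison of the two arms is not affected.

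**What to change.** State that any claim that a subgroup benefits more will rest on a treatment-by-subgroup (by time) interaction, with its lower-order terms, in the mixed model already planned. Fit it to all participants and retain the clustering. Report the difference in effects with its 95% CI at each analysed follow-up time, or at the primary time point once one is fixed; the article gives BMI at 3, 9 and 24 months without singling one out.

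Keep the stratum estimates as description only. Label the result exploratory, and say that power is about 31–45% even for an interaction of 0.7 kg/m², so that a non-significant interaction is not read as evidence of a uniform effect.

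The cost is wording in the analysis plan and a few extra model terms. No new data are needed. The 24-month collection is expected to finish around July 2027, so the change can be made before the final analysis.
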